### Outcome Measures

The primary clinical outcome measured daily in the app-enabled self-experiments is pain interference, measured using the modified Brief Pain Inventory 7-item interference subscale [19]. A change of 1 point in the average score across the 7 items is defined as clinically significant [20]. The secondary clinical outcomes are pain intensity, using a visual analog scale [21], and the number of additional treatments for pain flare-ups. All clinical outcomes are measured in the StudyU app.

In addition to these clinical outcomes, patients will also complete validated measures at baseline and 4 weeks following their self-experiment of self-efficacy, mental health, self-reported health status, health service use, and quality of life (refer to Table 1 for the full list of instruments used).

**Table 1 table1:** Summary of outcome measures.

Outcome type	Primary outcomes	Secondary outcomes and assessments
Clinical outcome measures	Primary clinical outcome (measured in StudyU app): pain interference (modified Brief Pain Inventory interference subscale) [19]	Secondary clinical outcomes (measured in StudyU app): pain severity [21] and use of additional treatments for pain flare-ups Measured pre– and post–self-experiment: pain self-efficacy (Pain self-efficacy Questionnaire) [22] Depression, anxiety, and stress (Depression Anxiety Stress Scale) [23] Health-related quality of life (Kemp QOL^a^ scale) [24] Self-reported health status Self-reported health care presentations in the previous 3 mo In patients with persistent neck or back pain following a road traffic crash: Neck Disability Index [25] and Oswestry Disability Index [26]
Evaluation of StudyU app	Surveys assessing technology usability, usefulness, and acceptance (1-question System Usability Scale) [27] Acceptability of StudyU (unified theory of acceptance and use of technology) [28]	Semistructured interviews with participants during follow-up Document participant experience with and feedback on the app Assess any perceived impact on their pain self-management Assess concordance of postexperiment behavior with StudyU results
Evaluation of self-experiments	Feasibility and acceptability outcomes Number of participants recruited and retained Baseline/postintervention response rates Number of self-experiments completed, and reasons for dropout Practice staff, GP^b^, and patient satisfaction with self-experiments	Process evaluation Structured interviews using Normalization Process Theory [29] 4 GPs, 4 practice nurses, and 10 patient participants to examine implementation barriers and enablers.

^a^QOL: quality of life.

^b^GP: general practitioner.

We will examine the feasibility and acceptability of integrating digitally enabled self-experiments over the 12 to 18 months study duration using a nested process evaluation and structured individual interviews informed by Normalization Process Theory [29], with study GPs and practice nurses following study completion. Patients will complete measures of technology acceptance and usability (Table 1) and participate in structured interviews after their self-experiments to explore their experiences. Feasibility outcome measures include the number of participants recruited and retained and the self-experiment completion rate. All management decisions and reasons for dropout will be recorded by the research team. Outcome measures are summarized in Table 1.

### Statistical Analyses

Both individual-level and population-level analyses will be conducted. To answer the primary research questions regarding feasibility and usability, we will analyze data collected across participants and provide descriptive statistics that summarize usability, usefulness, acceptability, and feasibility outcomes. To assess the effectiveness of clinical interventions at the individual level (ie, causal effects), we aim to test whether the primary and secondary clinical outcomes would differ between phases when the intervention was applied and when it was not applied (standard routine), for each individual separately. For this, we will perform *t* tests comparing average daily scores of primary and secondary clinical outcomes between usual routine and intervention phases, as well as Bayesian linear mixed models to calculate the posterior probability that the intervention is effective at the individual level. We will consider 2 definitions of treatment responders: having an estimated posterior probability higher than 80% of a reduction by at least 1 unit in pain interference (ie, in the average of the 7 items in the modified Brief Pain Inventory 7-item subscale [20]) and of any reduction in pain interference. It may be possible to perform these analyses at an aggregate level across patients if multiple participants test the same intervention. In all analyses, the primary analysis will assume that data are missing completely at random and will perform analyses of the complete-case data (for each individual separately) without imputation. Sensitivity analyses will test the robustness of the results after multiple imputation of missing data. For the clinical reports, we will report the results both from *t* tests and Bayesian linear mixed models. All analyses will be performed using the statistical software R (R Foundation for Statistical Computing). Structured interviews will be transcribed and analyzed thematically using template analysis [30].

As our primary aim is to evaluate the feasibility of embedding self-experiments in general practice, we did not perform statistical sample size calculations for study planning. Regarding the self-experiments, our primary aims are to test the feasibility of reporting the results to clinicians and patients. Regarding the reported results of the trials, the effectiveness of interventions will be tested at the individual level. For these analyses, 70 measurements (1 daily measurement for 10 weeks) will be available for each patient if there are no missing data. For a patient with 20% missing data, a 2-sided 2-sample *t* test at a significance level of .05 would have 80% power to identify treatment effects with an effect size of Cohen *d* of at least 0.53.

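### The per-patient two-sample t test treats consecutive daily ratings as independent; if they are positively autocorrelated, its false-positive rate exceeds the nominal 5%

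*Protocol article*

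**What the plan says.** The Statistical Analyses section of the protocol article plans *t* "tests comparing average daily scores of primary and secondary clinical outcomes between usual routine and intervention phases", run "for each individual separately", next to Bayesian linear mixed models. The power paragraph of that section gives the form of the test, "a 2-sided 2-sample" *t* test "at a significance level of .05", and takes days as the sample: "70 measurements (1 daily measurement for 10 weeks) will be available for each patient if there are no missing data".

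On reporting, the section says: "For the clinical reports, we will report the results both from *t* tests and Bayesian linear mixed models". The Introduction (Digitally Enabled Self-Experiments: StudyU) sends these reports to the patient and the GP. The Intervention section places the results in a follow-up GP consultation that includes a shared decision on continuing the activity.

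The same Intervention section describes an A1-B-A2 sequence over 10 weeks with 6 weeks in B. The Limitations section concedes that there is no randomization, blinding, within-case replication or check of baseline stability, and no blocks against wash-in or carryover. Serial correlation of the daily ratings is mentioned nowhere in the article.

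**The concern.** A two-sample t test estimates the standard error of the phase difference as if each day were a separate, independent observation. Here all days come from one person with persistent pain, and each condition occupies one or two unbroken runs of days. If a bad or good spell lasts several days, neighbouring ratings carry partly the same information. The phase means then vary more than the test assumes, and a slow fluctuation that happens to coincide with B can be declared significant too often.

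What is at stake is the individual report. The article describes the individual comparisons as causal, aims for patients to drop activities that do not work for them, and will assess whether later behaviour agrees with the StudyU result. A report that overstates its certainty weakens each of these uses.

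**Working it through.** **Inputs.**
- From Statistical Analyses: 70 daily ratings per patient, 20% missing in the power example, two-sided alpha of .05.
- From Intervention: B lasts 6 weeks = 42 days, so A1 + A2 = 70 − 42 = 28 days.
- From Setting and Participants: 30 expected completers.
- Assumed: A1 and A2 of 14 days each (the text does not give the split, and Figure 1 is not available), first-order autoregressive errors, and rho from 0 to 0.7. The article gives no rho.

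**Step 1: the plan's own figure.** The article claims 80% power for a standardised difference "of at least 0.53". With 20% missing, 0.8 × 70 = 56 days remain, about 22 in A (0.8 × 28 = 22.4) and 34 in B (0.8 × 42 = 33.6). The normal approximation for the detectable effect is 2.80 × √(1/22.4 + 1/33.6) = 2.80 × 0.273 = 0.76; the noncentral t gives 0.78. The stated 0.53 is not reproduced from 56 days in total. It appears with 56 days in each phase: 2.80 × √(2/56) = 0.53. That is a separate matter. What counts here is that any such calculation uses days as independent units.

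**Step 2: true variance of the phase difference.** Give each B day weight 1/42 and each A day weight −1/28 (vector c), and let R be the correlation matrix with entries rho^|i−j|. The ratio of the true variance to the one assumed by the t test is V = c′Rc / (1/42 + 1/28). The large-sample false-positive rate is 2 × [1 − Φ(1.96/√V)]. With no missing days:

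| rho | V | false-positive rate |
|---|---|---|
| 0 | 1.00 | 5.0% |
| 0.1 | 1.20 | 7.4% |
| 0.2 | 1.45 | 10.4% |
| 0.3 | 1.76 | 13.9% |
| 0.5 | 2.68 | 23.1% |
| 0.7 | 4.41 | 35.1% |

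Example at rho 0.5: 1.96/√2.676 = 1.198, and 2 × [1 − Φ(1.198)] = 0.231.

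**Step 3: simulation with 20% of days missing at random.** No effect, 14/42/14 days, pooled t test, 20,000 simulated patients per value of rho:

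| rho | 0 | 0.1 | 0.2 | 0.3 | 0.5 | 0.7 |
|---|---|---|---|---|---|---|
| rejected at .05 | 5.3% | 7.0% | 9.0% | 12.1% | 20.3% | 33.9% |

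Repeat runs agree within about one percentage point (for example 10% at 0.2, 13% at 0.3 and 21% at 0.5). Missing days thin the series, so these rates lie a little below those for complete data (24.5% at 0.5 and 38.2% at 0.7 in the same simulation).

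**Step 4: sensitivity.** At rho 0.5, Welch's test gives 21.1%, a 7/42/21 layout 20.8%, and a single 28-day A block before B 22.0%. The assumed split therefore matters little. Rho matters most: with rho = −0.1 the rate falls to 3.4%.

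**Step 5: reports affected.** About half of the rejections favour the intervention. At rho 0.5, 30 × 0.21 / 2 ≈ 3 no-effect completers would show a falsely significant benefit on one outcome. With independent days the figure is 30 × 0.025 = 0.75.

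**The case against.** Several points on the other side stand.

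- **Size is conditional.** The article gives no rho and no data from which to estimate one. The direction is firm for any positive rho. At rho 0.1 the excess is only about two percentage points, and the rate is well above 5% only from about rho 0.2.
- **Feasibility comes first.** The primary aim is feasibility and acceptability, summarised descriptively. Both responder definitions use the Bayesian posterior probability, so the t test affects neither.
- **Related weaknesses are disclosed.** The Limitations section warns of no randomization, no replication and no baseline-stability check, and says that caveats can be raised in the consultation. This covers part of the same inferential problem, though not the understated standard error.

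A reader might infer three stronger things that the document does not support. First, that the Bayesian model is overconfident in the same way: its residual structure is unstated, which a condensed article may leave to the full plan, so this is a point to confirm and not an error. Second, that p-values are sent to patients: the article says that t test results are reported and gives no format or significance rule for the reports; .05 appears only in the power sentence. Third, that about 6 of 30 completers would be told wrongly that their activity works at rho 0.5: that count includes rejections in both directions.

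The unseen full plan does not dispose of the core point. The article names the test and its form, and no further detail makes an ordinary two-sample t test valid for dependent days.

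**Conclusion.** The point holds in conditional form. The planned t test takes one patient's consecutive daily ratings, in long unrandomised blocks, as independent, and its results reach the patient and GP. If ratings are positively autocorrelated, the nominal 5% error rate is exceeded: about double at rho 0.2 and about four times at rho 0.5 with 20% of days missing. These sizes rest on assumed rho values, first-order autoregressive errors and a 14/42/14 layout; the direction needs only positive autocorrelation.

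This should be fixed, but it does not threaten the trial's primary conclusions. It still deserves action because reporting individual results to clinicians and patients is itself what the self-experiments are meant to test.

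**What to change.** In the individual analysis and the clinical report, replace the t test with a per-patient regression of the daily score on condition with AR(1) errors, for example generalised least squares in R. Alternatively, keep the t test comparison as descriptive only, with phase means and no claim of significance. State the residual correlation structure of the Bayesian model and confirm that it allows for serial correlation. A linear day term can be added as a sensitivity analysis; it need not be in the main model, and it would be strongly correlated with condition in a patient who continues the activity through A2.

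The cost is a few lines of code and a change of wording, with no new data collection. Intervals widen and fewer patients reach significance. With 70 complete days, the effect detectable with 80% power rises from d = 0.68 at rho 0 to about 0.82 at 0.2, 0.89 at 0.3, 1.05 at 0.5 and 1.15 at 0.7 with generalised least squares and known rho. The repair is not perfect, because rho must be estimated from a short series. In small simulations (600 to 1,000 patients per setting), false positives were about 4–5% at rho up to 0.3, 6–7% at 0.5 and 9–10% at 0.7, against about 21% and 34% for the t test at the last two values.

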### Digitally Enabled Self-Experiments: StudyU

The open access StudyU app is a mobile phone app designed for conducting single-case experimental designs [6]. In this study, we use the app to enable patients with persistent pain to evaluate the effectiveness of their choice of a self-management, nonpharmacological intervention. We have piloted the app with 4 community-based consumers with persistent pain. The app is embedded in the StudyU platform [6], which also includes a general-use tool for researchers and health care practitioners to design, monitor, and manage these patient self-experiments.

The StudyU app will generate daily reminders for patients to undertake their chosen activity, and rate pain severity and impact over a 10-week test period. After patients complete their self-experiments, the app will provide visual displays of daily ratings and average baseline vs intervention ratings, using color-coded bar graphs. The research team will also analyze outcomes using *t* tests and Bayesian linear mixed models to compare baseline and intervention conditions, producing clinical reports that are forwarded by a secure messaging system to the patient and their general practitioner (GP). StudyU does not require a user account and does not store any personal identifying data. The anonymized recorded study data will be published after study completion to contribute to an open worldwide data repository, with patient consent, to allow aggregation of single-case experiments testing similar interventions in future open science approaches, and to inform the design of future trials.

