#### Inclusion Criteria

Participants will be eligible for inclusion if they meet the following criteria: (1) aged >18 years; (2) currently experiencing clinically significant persistent pain for 3 months or longer, most days per week (average pain severity in last week of at least 3-4/10); and (3) on stable doses of regular pain medication (including medicinal cannabis) for ≥4 weeks prior or not currently taking pain medication.

A subgroup of participants will be recruited with an additional inclusion criterion of “persistent neck and/or back pain following a road traffic crash at least 3 months prior to recruitment.”

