#### Intervention

A research assistant embedded within the participating general practice will prepare and regularly update a list of low-cost activities generally recommended for the management of persistent pain and are locally available at low or no cost to practice patients. The activities are reviewed by a pain clinician to ensure they are generally appropriate. The list includes mindfulness practice, online pain management modules, low-impact exercise such as chair yoga or tai chi, walking programs (self-managed or group), and personalized or small group exercise programs. The patient selects an activity from this list with the approval of their GP. On receipt of the study referral, which is generated and autopopulated from existing practice software, the research assistant designs a personalized self-experiment for each patient using the StudyU Designer and forwards an invitation code to the patient for them to enter into the StudyU app to commence their personalized self-experiment.

Patients are assisted by the study team or practice nurses to download the StudyU app and enter their personalized invitation code. The patient’s self-experiment will continue for a total of 10 weeks, using an A1-B-A2 withdrawal/reversal single-case experimental design, where phase A1 is the patient’s usual or typical routine, phase B is 6 weeks of undertaking the intervention activity, and phase A2 is resumption of the usual routine (except for patients who wish to continue the intervention activity).

After the patient has completed their study, they will be encouraged to book a consultation with their GP to discuss the study results. This consultation will include shared decision-making about whether to continue the activity. Patients may also choose to conduct a second self-experiment with another activity.

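### Pooling A1 and A2 into one usual-routine mean discards the evidence from the reversal and can credit part of any early settling to the activity

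*Protocol article*

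**What the plan says.** The Intervention section describes each self-experiment as "using an A1-B-A2 withdrawal/reversal single-case experimental design" lasting 10 weeks. Its first two phases are set out as "usual or typical routine, phase B is 6 weeks of undertaking the intervention activity". For the third, the article returns the patient to the starting condition but allows an exemption: "phase A2 is resumption of the usual routine (except for patients who wish to continue the intervention activity").

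Statistical Analyses aims to assess the "effectiveness of clinical interventions at the individual level (ie, causal effects"). The t tests are described there as "comparing average daily scores of primary and secondary clinical outcomes between usual routine and intervention phases". A second method stands beside them and is introduced in these words: "as well as Bayesian linear mixed models to calculate the posterior probability that the intervention is effective at the individual level". A responder is a patient with a posterior probability above 80%, either of a reduction of at least 1 unit in pain interference or of any reduction. Results of both methods go into the clinical reports. The same section counts 70 daily measurements per patient for a two-sample t test.

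Entry requires "average pain severity in last week of at least 3-4/10" (Inclusion Criteria). The Introduction says that the app will show "visual displays of daily ratings and average baseline vs intervention ratings".

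The article does not say in so many words that A1 and A2 are merged. That follows from three statements taken together: both are usual routine, the test has two samples, and all 70 days are used.

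**The concern.** A withdrawal design earns its causal reading from two changes in sequence: improvement from A1 to B, then worsening from B to A2. One usual-routine mean set against one intervention mean ignores the order of the phases and so drops the second check.

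Two things can then go wrong for an individual patient.

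- A score that is high at entry and settles by itself lifts the A1 mean and appears as benefit.
- An effect that persists into A2, or an activity that the patient continues in A2, lowers the usual-routine mean and hides benefit.

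The pooled difference shows neither. The result goes to the patient and the GP as an individual effect and informs whether the activity is continued.

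**Working it through.** **The plan's own figure.** The plan gives no figure for this bias. Its one related number, a detectable Cohen d of 0.53 with 20% missing data, serves here only to show that all 70 days are used. It is reproduced with 56 days per phase (d = 0.53). With 0.8 × 70 = 56 days in total, split 22.4 to 33.6, d is 0.78. That is a separate matter, and nothing below depends on it.

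**Inputs from the article.** B = 6 weeks = 42 days. A1 + A2 = 10 − 6 = 4 weeks = 28 days. Responder cut-off 80%.

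**Assumed inputs.** A1 = A2 = 14 days (the text does not give the split; the figure is not shown). Excess at entry of D points, decaying as exp(−t/τ) from day 0, with τ = 7 days. Daily SD 1.5, independent days, flat prior, no treatment effect, no model terms beyond phase.

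**Step 1: bias from settling.** Phase means of exp(−t/7):

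- A1 (days 0–13): 0.464
- B (days 14–55): 0.024
- A2 (days 56–69): 0.000

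Pooled A − B = (0.464 + 0.000)/2 − 0.024 = 0.208 D. Separately, A1 − B = 0.440 D and A2 − B = −0.024 D. A real effect without carryover makes both positive. Here the second is about zero, which shows the artefact.

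Over other decay times the pooled bias is 0.12 D (τ = 3), 0.22 D (τ = 10, about the maximum) and 0.09 D (τ = 42).

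**Step 2: false labels.** SE = 1.5 × √(1/28 + 1/42) = 0.366.

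- Any reduction: P = 1 − Φ(0.842 − bias/SE)
- At least 1 unit: P = 1 − Φ(0.842 + (1 − bias)/SE)
- t test significant for benefit (normal approximation): P = 1 − Φ(1.96 − bias/SE)

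| D | Bias | Any reduction | At least 1 unit | t test |
|---|---|---|---|---|
| 0 | 0 | 20% | <0.1% | 2.5% |
| 0.5 | 0.10 | 29% | <0.1% | 4.7% |
| 1.0 | 0.21 | 39% | 0.1% | 8.2% |
| 1.5 | 0.31 | 50% | 0.3% | 13% |

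The 20% at D = 0 follows from the 80% cut-off itself. With A1/A2 = 7/21 days the bias is 0.104 D, giving 29% and 34% for D = 1.0 and 1.5. With 21/7 it is 0.246 D, giving 43% and 57%. With 7/21 and slow decay the sign reverses (−0.05 D at τ = 21).

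**Step 3: linear trend.** The mean day is 6.5 in A1, 34.5 in B and 62.5 in A2. Pooled A has mean day (6.5 + 62.5)/2 = 34.5, the same as B, so a straight-line trend cancels. Without A2 the gap is 34.5 − 6.5 = 28 days, and a drift of −0.02 points per day gives 28 × 0.02 = 0.56 points of false benefit. For a fall of 1 point over the 10 weeks, the bias is −0.254 with 7/21 and +0.254 with 21/7.

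**Step 4: carryover.** If a true 1-unit effect persists fully through A2, A1 − B = 1 and A2 − B = 0, so the pooled effect is (1 + 0)/2 = 0.50. The same holds if the activity continues in A2 and those days are counted as usual routine.

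**The case against.** The strongest reply is that this is a feasibility study, that the article is condensed, and that the design's weaknesses are disclosed. The Limitations section concedes no baseline-stability assessment, no replication and no blocks against wash-in or wash-out, and leaves caveats to the GP consultation. The app also shows daily ratings, so an absent reversal may be visible. All of this stands. However, Limitations names neither regression to the mean nor the pooling, and its argument against longer experiments does not apply to a change that adds no days.

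The size is also open to challenge. Selection is on severity, while the primary outcome is interference. Patients must have had pain for at least 3 months and be on stable medication or none. Referral and set-up come between screening and A1, so some settling may be over by day 1. The excess is therefore an assumption and may be small; severity is, though, itself a secondary outcome tested in the same way.

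Some stronger readings are tempting, but the documents do not support them:

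- *No analysis adjusts for time.* This is certain only for the t test. The Bayesian model's terms are not given and may be in a fuller plan.
- *A missing time term causes the settling bias.* With equal, complete A phases a linear day term is orthogonal to phase. At τ = 10 the bias is 0.223 D with or without it.
- *All regression to the mean is credited to the activity.* At 14/14 days under exponential decay it is at most about 0.22 of the excess.
- *The 20% missing data could be all of A2.* That figure is a power illustration, and the primary analysis assumes data missing completely at random. The better-founded worry is the permission to continue the activity in A2.
- *Only patients passing both contrasts should count as responders.* In simulation under the Step 2 settings this cut false labels from 39–50% to 13–15%, but it also passes only about 6% instead of 20% when there is no excess. The gain is thus largely stringency, and patients with genuine carryover lose the label.

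**Conclusion.** The concern holds in limited form. The stated t test, read naturally, pools A1 with A2 and so does not use the reversal that the design provides. If there is early settling, about a fifth of the entry excess is reported as benefit (14/14 days, τ of 7 to 10 days). This matters for the any-reduction label and hardly at all for the 1-unit label. A linear trend cancels only if A1 and A2 are equal, equally observed and A2 is a true withdrawal, which the Intervention section does not ensure. Full carryover halves the pooled effect.

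The pooling is inferred. The phase split, the size and decay of the excess, the SD and the independence of days are assumptions. The responder percentages also assume that the Bayesian model has no terms that would change the contrast. This is a worthwhile, inexpensive improvement to individual reporting and does not undermine the feasibility aims.

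**What to change.** In the analyses and clinical reports:

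- Give A1-B and B-A2 as separate contrasts beside the pooled one.
- Attach 'reversal seen' or 'reversal not seen' to the any-reduction label, as information and not as a condition for being a responder. Explain that 'not seen' fits either settling or carryover; the phase means alone do not tell them apart.
- Where A2 is missing or the activity was continued, report 'reversal not tested' and do not count those days as usual routine.
- State whether the Bayesian model has a time term. A linear day term helps when A1 and A2 are unequal or incomplete, but it does not cure early settling.

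Cost: no new data, only analysis code and slightly longer reports. The separate contrasts are less precise: √(1/14 + 1/42) = 0.309 SD against √(1/28 + 1/42) = 0.244 SD, so intervals are about 26% wider at 14/42/14 days.

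### The stated detectable effect of Cohen d 0.53 does not follow from 56 ratings per patient; the design gives about d 0.78, and power at 0.53 is about 48%

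*Protocol article*

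**What the plan says.** The last paragraph of Statistical Analyses explains that no sample size calculation was done for study planning because the primary aim is feasibility. It then turns to the self-experiments, for which "the effectiveness of interventions will be tested at the individual level". The information available is described as follows: "70 measurements (1 daily measurement for 10 weeks) will be available for each patient if there are no missing data". The sensitivity claim is made "For a patient with 20% missing data", for "a 2-sided 2-sample *t* test at a significance level of .05", which "would have 80% power to identify treatment effects with an effect size of Cohen *d* of at least 0.53".

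The Intervention section sets out a 10-week A1-B-A2 experiment in which "phase B is 6 weeks of undertaking the intervention activity". That leaves four weeks for the two usual-routine phases together. The first paragraph of Statistical Analyses says that the t test compares usual-routine with intervention days, separately for each individual, and that its result goes into the clinical report beside the Bayesian result.

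**The concern.** The 70 ratings are a total over both conditions, and a two-sample test has to divide them. With 56 ratings left, neither condition can have more than about 34, and a two-sample test of that size does not usually detect half a standard deviation with 80% power. The printed effect size looks like the answer for a sample about twice as large.

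This is the article's only statement of what a single self-experiment can detect. The t-test results go to the patient and the GP, who then decide together whether to continue the activity. The Aim section includes helping patients to discontinue treatments that do not work for them personally. A reader who trusts the stated 80% would take a non-significant t test as fairly good evidence against a medium-sized effect, when the test would miss that effect about half the time. The error is in the favourable direction.

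**Working it through.** **Inputs**

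- Two-sided alpha .05, power 80%, two-sample t test, 20% missing (Statistical Analyses).
- 70 ratings in total per patient (Statistical Analyses). After 20% loss: 70 × 0.8 = 56.
- Phase B is 6 of 10 weeks (Intervention): 42 days of intervention and 70 − 42 = 28 days of usual routine. After 20% loss: 42 × 0.8 = 33.6 and 28 × 0.8 = 22.4.
- Cohen d is standardised, so no standard deviation is needed.

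**Formula**

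In the normal approximation, the effect detectable with 80% power is d = (1.960 + 0.842) × √(1/n₁ + 1/n₂) = 2.802 × √(1/n₁ + 1/n₂). The exact values below use the noncentral t distribution and are slightly larger.

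**Reproducing the stated 0.53**

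With 56 ratings in each condition: 2.802 × √(2/56) = 2.802 × 0.1890 = 0.529; exact 0.534. Both round to the printed 0.53. This needs 112 ratings, and the design has 70 at most.

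**The design's own numbers**

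With 22.4 and 33.6 ratings: √(1/22.4 + 1/33.6) = √(0.0446 + 0.0298) = 0.2728, and 2.802 × 0.2728 = 0.764; exact 0.778.

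Power at d = 0.53: 0.53 / 0.2728 = 1.943, and Φ(1.943 − 1.960) = 0.493; exact 0.479.

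| Usual routine / intervention | Detectable d, normal | Detectable d, exact | Power at d = 0.53, exact |
|---|---|---|---|
| 22.4 / 33.6 (design, 20% missing) | 0.764 | 0.778 | 48% |
| 22 / 34 (whole numbers) | 0.767 | 0.781 | 48% |
| 28 / 28 (even split of 56) | 0.749 | 0.762 | 50% |
| 28 / 42 (no missing data) | 0.684 | 0.693 | 57% |
| 56 / 56 (not available) | 0.529 | 0.534 | 79% |

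**Other readings tried**

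- A one-sided test on 56 ratings in total gives 0.673 (28/28) or 0.687 (22.4/33.6).
- A paired or one-sample test with n = 28 gives 0.549. That is not the stated test and would round to 0.55.
- At the 3:2 split, 80% power at d = 0.53 needs about 118 non-missing ratings; 56 are available.

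**Two features that make 0.78 optimistic**

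- *Autocorrelation.* The calculation treats days as independent. The article gives no autocorrelation, so the values here are assumptions: first-order autoregressive ratings, A1 and A2 of two weeks each, 20% missing at random and a standard error that allows for the correlation. The detectable effect (normal approximation) is then about 0.97 SD at a lag-1 correlation of 0.3 and about 1.17 SD at 0.5.
- *Continuing the activity in A2.* The Intervention section lets patients do this. If only A1 then counts as usual routine, and A1 is assumed to be two weeks, 14 × 0.8 = 11.2 ratings face 33.6. The detectable d is 0.99 and power at 0.53 is 32%.

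**The case against.** The arithmetic is not in dispute; the case on the other side is that little depends on it. The study is a feasibility study, and its main questions are answered descriptively. The recruitment target is justified as adequate for a feasibility study, and the decision not to lengthen the experiments is explained in Limitations by patient engagement. No design quantity is derived from d = 0.53. Correcting it changes no patient's estimate, p value or posterior probability. Responders are defined by posterior probabilities from the Bayesian model, and no rule ties stopping an activity to a non-significant t test. Continuation is a shared decision in a consultation where caveats can be raised.

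Much of this stands, and it limits the consequences. The article does not say that the power figure itself appears in the clinical reports, so harm through those reports is a risk rather than a certainty. That 56 was entered as the size of each group is also an inference, though a close one.

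None of this makes the sentence correct. The article chose to state a specific power for the individual tests, and those tests are reported to patients and GPs alongside the Bayesian results. No sensitivity figure is given for the Bayesian analysis, which draws on the same ratings. Limitations discusses delayed onset, carryover, replication and blinding, but not the low power of the individual tests. This is also not a detail left to an analysis plan: it is a printed figure that the article's own inputs contradict.

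**Conclusion.** The statement is wrong as written. With 56 ratings in total at the 3:2 split, the t test has 80% power for d of about 0.78, which is 47% larger than stated (0.778 / 0.53 = 1.47). At d = 0.53 its power is about 48%, not 80%. The conclusion does not depend on the split or on the missing data: an even split gives 0.76 and complete data give 0.69.

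The figure of 0.78 assumes independent daily ratings and that A1 and A2 both count as usual routine and fill the four weeks outside phase B. If ratings are positively autocorrelated, or if a patient continues the activity in A2, the detectable effect is larger. The autocorrelation figures rest on assumed values and only indicate direction and rough size; the finding does not need them.

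**What to change.** Replace the power sentence in Statistical Analyses with wording such as:

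> With 20% missing data (about 22 usual-routine and 34 intervention ratings), a 2-sided 2-sample t test at .05 has 80% power for d of about 0.78 if days are independent, and for a larger effect if daily ratings are autocorrelated.

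Add a clause saying that the 22 usual-routine ratings presuppose a return to usual routine in A2. If the clinical reports carry a caveat on what the t test could have detected, base it on the corrected figure, so that a non-significant result is not read as good evidence of no effect.

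The cost is one sentence in the article, plus the matching caveat in the report text. The stated sensitivity becomes less favourable. Recruitment, study procedures, data collection and analyses stay as they are.
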